### Data analyses

The study will obtain estimates of the leadership intervention effect by comparing multiple intervention measures on provider-rated leadership, workplace climate, work attitudes, and attitudes toward adopting and implementing EBPs. The workgroup will be the unit of analysis, with sites randomized within agency to ensure that the 5% of co-located workgroups will be randomized into the same condition to avoid contamination. For 95% of workgroups, workgroup is synonymous with site. We will stratify by the number of workgroups per site to ensure equal workgroups in each condition.

Data analytic strategies will follow the recommendations of Brown et al. [85] and the Prevention Science and Methodology Group for randomized field trials [86]. Preliminary data screening and cleaning will require examination of data distributions for normality and missing data patterns at both the univariate and multivariate levels. Once complete, hierarchical linear modeling (HLM) [87] will be used as the primary statistical model due to the nested structure of the data: repeated measures (time) (level-1) nested within service providers (level-2) nested within workgroups (level 3). Because randomization is at the workgroup level, and due to the statistical complications associated with the small number of agencies and a number of workgroups being located at the same site, dummy-coded agency and site variables will be entered at the level of the workgroups for all analyses, which implicitly controls for agency and site effects [88]. Random effect variance will be evaluated for the remaining levels of the nested data structure. In the presence of near zero estimates of variance estimates, terms will be removed from the statistical model.

HLM analyses for aims 1 and 2 will test specific intervention effects (LOCI vs. webinar control condition) on target outcomes (e.g., leadership behaviors, implementation climate). Of primary interest in these analyses is the Time (level-1) × Intervention Status (level-3) cross-level interaction effect. If the cross-level interaction term(s) are statistically significant, follow-up examination of these effects will follow the procedures of Preacher, Curran, and Bauer [89]. Implementation of cross-classified models will be explored given that some shifting or personnel may occur during the course of the study [90].

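### The rule for removing near-zero variance terms should exempt the workgroup level, because the Time × Intervention test needs between-workgroup variance in change

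*Protocol article*

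**What the plan says.** Everything relevant is in the Data analyses section of the protocol article. The model has three levels: occasions within service providers within workgroups. Agency and site are handled as fixed effects: "dummy-coded agency and site variables will be entered at the level of the workgroups for all analyses". For what is left, "Random effect variance will be evaluated for the remaining levels of the nested data structure", followed by the rule in question: "In the presence of near zero estimates of variance estimates, terms will be removed from the statistical model".

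The test that carries Aims 1 and 2 is then named: "Of primary interest in these analyses is the Time (level-1) × Intervention Status (level-3) cross-level interaction effect". The same section places allocation at the cluster ("Because randomization is at the workgroup level") and declares the workgroup the unit of analysis.

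The section gives no numerical meaning of near zero, no scale on which it is judged, no coding of time and no list of random terms. In particular, it does not say whether a random slope for time is planned at workgroup or provider level.

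**The concern.** LOCI is assigned to workgroups, and its effect is read from the difference in change over time. Workgroups will differ in how much they change for reasons unrelated to LOCI, and that spread is part of the sampling error of the Time × Intervention estimate. In a mixed model it enters as the workgroup-level random slope. Without that term, the standard error treats providers (or, if provider slopes are also absent, occasions) as independent replicates, although the article declares the workgroup as the unit.

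The rule permits this outcome on the strength of an estimate. It covers every remaining level and protects none. H1a, H1b and H2a–H2d all rest on this test, so the stake is whether their nominal error rate and interval widths can be relied on.

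**Working it through.** **No figure to reproduce.** The article gives no alpha, power, intraclass correlation or variance threshold, so the check asks how the rule behaves under stated assumptions.

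**Inputs from the article.** 60 workgroups and about 360 providers, so 360/60 = 6 per workgroup. Equal allocation gives 30 per arm. Waves are at 0, 4, 8, 12 and 16 months. Most survey outcomes are on 0–4 scales.

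**Assumptions.** Two-sided 5% test, linear time coded in months, complete data, residual variance 0.4, and a true SD of 12-month change between workgroups of 0.1, 0.2 or 0.3 points.

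**Step 1: variance of a provider's slope.** The mean wave time is 8, so Sxx = 64 + 16 + 0 + 16 + 64 = 160. Sampling variance of one provider's slope = 0.4/160 = 0.0025.

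**Step 2: workgroup slope variance.** τ² = (SD/12)². This gives 0.000069, 0.000278 and 0.000625. As a share of provider-slope variance, ρ = τ²/(τ² + 0.0025) = 0.027, 0.10 and 0.20. A material spread in change is therefore a very small number on the raw monthly scale.

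**Step 3: if the workgroup slope is absent altogether.** With providers as the units, the true standard error exceeds the one used by a factor of √(1 + 5ρ), and type I error = 2·(1 − Φ(1.96/√(1 + 5ρ))).
- SD 0.1: √1.135 = 1.065, about 6.6%
- SD 0.2: √1.5 = 1.225, about 11.0%
- SD 0.3: √2 = 1.414, about 16.6%

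**Step 4: if the slope is planned and the removal rule is applied.** This was simulated under no LOCI effect, with 100,000 to 200,000 trials per setting. A kept term is tested on workgroup mean slopes with 60 − 2 = 58 df. A removed term gives a provider-level test with 360 − 2 = 358 df. Overall type I error:

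| True SD of 12-month change | Always kept | Removed if estimate ≤ 0 | Removed if not significant at 5% | Removed if raw variance < 0.001 |
|---|---|---|---|---|
| 0.1 | about 5% | 4.8% | 5.9% | 6.6% |
| 0.2 | about 5% | 4.9% | 5.5% | 10.9% |
| 0.3 | about 5% | 5.0% | 5.1% | 16.1% |

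The columns differ because of how often the term goes. At SD 0.2 the estimate is at or below zero in about 1% of trials, and at SD 0.3 practically never. With the raw cut-off of 0.001 it is removed in about 100% and 96% of trials.

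**Step 5: sensitivity.** A cut-off on estimated ρ of 0.05 gives at most 5.8%, and one of 0.10 at most 7.4%. A raw cut-off of 0.0005 at SD 0.3 gives 7.8%. If provider slopes are not in the model either, the raw cut-off of 0.001 gives 12.3% at SD 0.2 and 19.5% at SD 0.3.

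**The case against.** Four points can be made on the other side.

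**A rule that removes only near-zero estimates rarely removes a term that matters.** This largely stands. A reader might infer that the rule itself brings error rates of about 7%, 13% and 21% at SDs of 0.1, 0.2 and 0.3. These follow from a term that is always dropped with no provider slope: naive variance 2 × 0.4/160/180, true variance larger by 2τ²/30, standard-error ratios 1.08, 1.29 and 1.58. The article does not say that the term is always dropped, and under a strict reading of the rule the level holds at about 5%.

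**The unfavourable case needs a particular reading.** Someone must judge the variance on its raw size with time in months. The article states neither. It does not exclude them either, and the sentence speaks of variance estimates rather than of a share or a test.

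**No workgroup slope is named, so its deletion is an inference.** This is correct. A reader should not conclude that a planned slope will be deleted. If none was planned, however, the test is exposed directly, at the rates in Step 3. The structure and a cut-off may also be set out in a fuller plan that is not shown.

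**The site indicators.** Because "For 95% of workgroups, workgroup is synonymous with site", a reader might infer that the site dummies make matters worse. They absorb workgroup differences in level. They are not described as interacting with time, so they leave differences in slope alone and do not bear on this test in that way.

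**Conclusion.** The point holds as a conditional one. The article states a data-driven removal rule with no cut-off and no protection for the randomized level, while its main test depends on variance at that level. Under the assumptions listed, overall type I error is about 5% if only estimates at or below zero are removed. It is at most about 6% if non-significant terms are removed. It is about 11–16%, for a true SD of 12-month change of 0.2–0.3 points and with provider slopes kept, if a raw monthly variance below 0.001 counts as near zero. Never including the slope gives similar figures, 11.0–16.6%.

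The article fixes none of the residual variance, the between-workgroup spread, the alpha or the cut-offs, so these figures show a range of consequences and do not predict the trial's error rate. The documents do not support saying that the 5% level will fail. They support saying that the rule as worded does not guarantee it. Given the low cost of closing the gap, this is a worthwhile improvement rather than a must-fix.

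**What to change.** Change the removal sentence so that, in the Aim 1 and 2 models, the workgroup-level random intercept and random time slope are kept whatever their estimates, and Time × Intervention is tested on workgroup-based degrees of freedom. Only provider-level terms may be simplified. If the model cannot be fitted, analyse workgroup-level change scores instead. Kenward–Roger is one way to obtain the degrees of freedom, but it is optional.

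The cost is one sentence and slightly conservative inference when the true workgroup variance is zero. In the balanced calculation, keeping the term with its estimate bounded at zero and 58 df gave type I error of 4.0–5.1% for ρ from 0 to 0.20.

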## Discussion

LOCI has been developed to be feasible and effective for organizations to create a positive climate and fertile context for EBP implementation. The approach seeks to cultivate and sustain both effective general and implementation leadership in conjunction with organizational strategies and supports that will remain after the implementation strategy has ended. LOCI’s strategic in-person training combined with brief weekly coaching minimizes burden and promotes ongoing cognitive processing (i.e., being mindful of leadership and implementation issues) and enables ongoing and repeated efforts at behavior change. Effective leadership in health and allied health services is associated with more positive staff attitudes toward adopting EBP, provider adoption of EBPs, improved staff work attitudes, and performance [51]. Effective leadership is also critical in the successful and sustainable implementation of innovation [31, 92]. LOCI builds on these findings to garner broader organizational stuructures and processes to support implementation and sustainment.

Most agencies already provide manager trainings, but these tend to be more superficial and lack follow-up to support leader and organizational behavior change. There are many off-the-shelf leadership development programs, but such programs may lack utility because (1) they tend to be broad in scope and not designed to develop strategic climates for EBP, (2) are often not based on empirically supported approaches and curricula, (3) are often time-limited with little or no follow-up and inconsistent with learning theory that suggests interventions distributed over time and coupled with coaching and practice are more effective [93], and (4) are rarely tested for evidence of effectiveness or practical utility. The work proposed in this study addresses each of these limitations by (1) focusing on developing strategic climate for EBP in SUDT services, (2) utilizing an empirically based curriculum with measurable outcomes [94], (3) combining didactic and interactive training with ongoing coaching to support learning and behavior change, (4) linking first-level leader development with targeted organizational support strategies, and (5) empirically testing LOCI to determine its effects on proximal (leadership behaviors, implementation climate) and distal (provider attitudes and behaviors, fidelity, implementation process) outcomes.

While many SUDT providers are trained in MI, few deliver MI with fidelity. This study addresses a major gap in the way in which EBPs are “implemented” in usual care SUDT settings. It is not enough to “train and hope” that EBPs will be delivered with fidelity and in a manner that will lead to improved patient outcomes. What is needed are more comprehensive approaches to changing the context of community-based services to be ready, willing, and able to implement appropriate evidence-based service models to improve patient outcomes. The LOCI intervention holds promise in regard to these goals.
